### Sample size {14}

A sample size of twenty-four (*n* = 12 per group) provides 80% power to detect a 50% difference in proportions of participants between groups by chi-squared test experiencing a laboratory abnormality or adverse event at a significance threshold of *α* = 0.05. To account for up to 25% attrition, up to 16 adults (8 biologically male and 8 biologically female participants) will be enrolled in each study arm. Given that this phase I trial is intended as a step toward a phase II clinical trial in Crohn’s disease, for which few effective treatments exist, the investigational drug is commonly available in the diet, and previous human studies have not suggested any toxicity, the present trial was powered to detect gross toxicity resulting in frequent adverse events and/or laboratory-measurable toxicity. However, interim halting criteria were also used to assess safety; an accumulated frequency of 25% reaching laboratory halting criteria was pre-specified as a criterion for halting the trial and requiring detailed review by the FDA, NCCIH, and IRB.

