## Assignment of interventions: allocation

### Sequence generation {16a}, concealment mechanism {16b}, implementation {16c}, blinding {17a}, and unblinding {17b}

Randomization will occur within 30 days of screening by blocking within the randomization sequence, with randomization stratified by biological sex. The initial randomization series will be generated using readily available electronic random sequence generators. The randomization “code” will be created by a staff member not involved in trial operations and kept in a sealed envelope with a signature across the label and dated the day of creation. This envelope will be kept in a dedicated study folder and locked in the office of the Research Integrity Officer or designee. Thirty-two opaque envelopes will be created, sequentially numbered include a designation of the code for the assigned intervention based on the randomization sequence, and signed across the seal. Masking of the interventions (i.e., xanthohumol or placebo) will be accomplished by engaging trained staff not involved in trial operations to label product bottles based on the randomization code. Product bottles will be stored in separate locked cabinets by code and maintained in a temperature-controlled environment, with temperature logged weekly to assess environmental stability. Upon confirmation of eligibility and consent, Study Coordinators will then open the next sequentially numbered envelope at the time of randomization, the envelope number will be recorded, and allocation (As “A” or “B”) disclosed to both participant and coordinator for the first time, and the corresponding product will be removed from its locker and dispensed in the bottle to the participant. Thus, the trial will be triple-masked without PIs, co-investigators, study coordinators, or participants knowing allocation assignment of study participants. Unmasking is permissible if the DSMB requires it upon review and in the case of a serious adverse event.

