### Laboratory analysis outcomes {12}, statistical methods {20a, 20b, 20c}

Relevant laboratory-based safety measures were chosen as the primary safety outcomes, because this trial is intended to precede a clinical trial in adults with Crohn’s disease—a clinical population potentially vulnerable to anemia, liver toxicity, renal abnormalities, etc. Therefore, a formal assessment of laboratory changes in healthy humans provides critical information to guide expectations for changes in laboratory markers and associated adverse clinical effects in future research in Crohn’s and other clinical populations.

The primary objective’s laboratory-based outcome domains (and corresponding measures) are liver function (AST, ALT, alkaline phosphatase, bilirubin), renal function (BUN, creatinine, estimated glomerular filtration rate), hematology (red blood cell count, hematocrit, hemoglobin, white blood cell count), and electrolytes (sodium, potassium, calcium, chloride) measured every 2 weeks for 8 weeks. The primary outcome metric for comparison between study groups is the mean change from baseline to week 8. However, all parameters will be similarly evaluated at each follow-up time point, by formally comparing mean change from baseline to follow-up between groups. Comparisons at a single follow-up will use 2-sided independent *t* tests; omnibus tests for differing trends over time will employ linear mixed models with time point as a repeated factor and study group as an independent factor.

Primary outcome laboratory measures will be analyzed by first assessing descriptive statistics including mean, median, and standard deviation. All distributions will be tested for skew and transformed (e.g., natural log transformed) as needed to reduce the influence of skew in subsequent analyses. If inspection of distributions indicates significant non-normality that cannot be corrected with standard transformations, significance will instead be calculated using a non-parametric Wilcoxon signed rank test. The primary analysis will be a per-protocol analysis as this trial is a phase I trial focused on clinical toxicity, not a definitive efficacy or effectiveness trial; therefore, we are investigating the clinical and mechanistic effects of the product for those participants who took the experimental agent only. As a sensitivity analysis, missing laboratory data will be imputed by multiple imputation to assess the robustness of study results to imputation.

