As an element of the evaluation for safety of the intervention, the percentage of laboratory newly abnormal (for values that were within the clinically normal range at baseline) per clinical laboratory reference ranges for each lab parameter will be reported at each time point and the percentage will be compared between groups by Fisher’s exact test. Assessment for changes in the distribution of each lab parameter will be performed by presenting means and confidence intervals (CI) for the change in each group, as well as the mean CI for the difference between groups; significance will be tested using 2-sided, unpaired *t* tests (or, if inspection of distributions indicates strong non-normality, with a non-parametric Wilcoxon signed rank test) of the mean values for the xanthohumol group compared to the placebo group. Assessment for overall *increases* or *decreases* in collected parameters will be tested for linear trends of the means by linear mixed ANOVA, considered significant if *p* < 0.05, with time point as a repeated factor. This may be suggestive of evidence for cumulative toxicity if trending in a clinically deleterious direction.

Health-related quality of life, measured by PROMIS-29, is included as a tertiary measure of gross changes in health. PROMIS-29 includes 7 validated subscales (physical function, anxiety, depression, pain intensity, pain interference, sleep, social interactions), each of which will be calculated as a mean by group, and means will be compared between xanthohumol and placebo, with the primary comparison being of mean changes from baseline to week 8. Significance of changes in QOL measures will be tested according to the same plan outlined for laboratory markers, above.

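### Laboratory change-score t tests are valid but forgo precision by not adjusting for baseline and sex, and the cumulative-toxicity trend reading is not tied to a between-group contrast

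*Protocol article*

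**What the plan says.** All the analysis text is in the protocol article, section Laboratory analysis outcomes {12}, statistical methods {20a, 20b, 20c}.

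- **Week-8 and single-visit comparisons.** The primary metric is mean change from baseline to week 8, with each earlier follow-up treated the same way. "Comparisons at a single follow-up will use 2-sided independent" t tests. A later paragraph repeats the unpaired t test. Neither place names a covariate.
- **Randomization.** The allocation section (items 16a to 17b) describes blocking, "with randomization stratified by biological sex".
- **Between-group trend.** The same paragraph as the t tests plans an omnibus linear mixed model for differing trends over time, with time point as a repeated factor and study group as a factor.
- **Overall trend.** The following page of text says that increases or decreases in the parameters "will be tested for linear trends of the means by linear mixed ANOVA", at p < 0.05. Time point is the only factor named. It then adds: "This may be suggestive of evidence for cumulative toxicity if trending in a clinically deleterious direction".

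The PROMIS-29 comparisons follow the laboratory plan, and the cytokine and gut-permeability comparisons also use change from baseline, so the first point carries over to them.

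**The concern.** There are two separate issues.

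**Precision.** Every laboratory measure has a baseline value and sex is known for everyone. In a trial this small, a comparison that conditions on both uses data already collected and can sharpen the estimate. The article does not leave this open: it names the unadjusted test.

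**Meaning of the trend test.** A test of time alone asks whether the measure moves during the study, not whether it moves differently on xanthohumol. Blood is drawn every 2 weeks in both arms, and season, laboratory calibration or study participation could also move both arms together. Falling haemoglobin from repeated draws is an illustration only; the article gives no blood volume. As written, such shared movement meets the condition under which cumulative toxicity is suggested, although the placebo arm would show that the product was not the cause.

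**Working it through.** **Inputs from the article.** "A sample size of twenty-four (*n* = 12 per group"); "To account for up to 25% attrition, up to 16 adults" per arm; 1:1 allocation; measurements every 2 weeks for 8 weeks, so five visits including baseline; two-sided tests at 0.05.

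**Assumed, because the article gives no figure.** The correlation r between a participant's values at two visits; equal SD (set to 1) at every visit; the size of any drift shared by both arms.

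**The plan's own sample size.** The article states that this number "provides 80% power to detect a 50% difference in proportions of participants between groups by chi-squared test", without a control rate. With the usual pooled-variance formula, 5% against 55% gives 12 per arm (power 80.2%), so the figure reproduces for a low control rate. At 0% against 50% it is 11, and at 25% against 75% it is 15. Attrition: 12/(1 − 0.25) = 16. This calculation concerns proportions, and the points below do not affect it.

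**1. Change score against analysis of covariance**

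- Variance of the change score: 2(1 − r).
- Residual variance after conditioning on baseline: 1 − r².
- Ratio: (1 − r²)/[2(1 − r)] = (1 + r)/2.

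At 12 per arm, the t test on change (22 df) has 80% power for a difference of 1.197 SDs of the change score, that is 1.197 × √[2(1 − r)] on the scale of the measure. For the adjusted analysis, the variance is multiplied by 1 + 1/(2n − 4) = 1.05 to allow for estimating the baseline slope (21 df).

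| r (assumed) | Variance ratio | Detectable difference, change score | Detectable difference, adjusted | Adjusted power where change score has 80% |
|---|---|---|---|---|
| 0.5 | 0.75 | 1.20 SD | 1.06 SD | 88% |
| 0.7 | 0.85 | 0.93 SD | 0.88 SD | 84% |
| 0.8 | 0.90 | 0.76 SD | 0.74 SD | 82% |
| 0.9 | 0.95 | 0.54 SD | 0.54 SD | 80% |

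A simulation (5,000 trials per setting) with baseline and sex both in the model gave 87.4%, 83.6%, 82.0% and 80.1%. Under no effect, both methods rejected in about 5% of trials. Sex had no effect on outcome in that simulation, so it shows only that including sex costs almost nothing. It does not show a gain from it.

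**2. Time-only trend against group-by-time trend**

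Visits at weeks 0, 2, 4, 6 and 8 have centred times −4, −2, 0, 2 and 4, with sum of squares 40. At r = 0.7 (the same correlation between all pairs of visits):

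- SD of one participant's estimated 8-week movement: 8 × √(0.3/40) = 0.693.
- Standard error of the mean movement over all 24 participants: 0.693/√24 = 0.141.
- Standard error of the difference between arms: 0.693 × √(2/12) = 0.283.

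A shared drift of 0.3 SD is 0.3/0.141 = 2.1 standard errors for the time-only test, and zero for the difference between arms. Proportion of 20,000 simulated trials significant, with no product effect:

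| Shared drift over 8 weeks (assumed) | Time only | Group by time |
|---|---|---|
| 0 | 5% | 5% |
| 0.2 SD | 28% | 5% |
| 0.3 SD | 53% | 5% |
| 0.5 SD | 92% | 5% |

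For a drift of 0.3 SD, varying r from 0.6 to 0.8 moves the time-only figure from 42% to 70%. If the sentence is read as a test within the xanthohumol arm alone, the standard error is 0.693/√12 = 0.200, and drifts of 0.3 and 0.5 SD are significant in 28% and 62% of trials.

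The reverse case also matters. If only the xanthohumol arm moves, by 0.5 or 0.8 SD, the pooled time-only test detects it in 35% and 67% of trials and the group-by-time test in 39% and 77%. Relative to the pooled test, the between-group contrast therefore loses no sensitivity here.

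**The case against.** The strongest defence of the t test is that nothing is wrong with it. Under randomization it is unbiased and holds its error rate. The change score already removes each participant's own level, including any stable difference between the sexes, and stratified blocking promotes balance by sex. Newly abnormal values, adverse events and confidence intervals for change stand beside it. All of this stands, and it makes the first point one of efficiency.

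A reader might infer that the plan ignores baseline, or that chance imbalance biases the result. The article does not support either. Baseline is subtracted, and although a particular imbalance can shift the estimate in one trial, this averages out over randomizations and is already reflected in the test's standard error.

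On the trend, the defence is that the article plans a mixed model with study group, that the toxicity sentence is hedged, and that neither the suspension nor the halting criteria use it. This also stands. A reader might infer that the plan has no between-group trend test, or that it has a rule declaring shared drift to be toxicity; neither is so. What remains is that the toxicity reading is attached to the test that names only time, and nothing directs the reader to the model that could answer the question.

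**Conclusion.** The point holds in two limited parts.

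First, the unadjusted comparison gives up precision only. How much depends on r: worthwhile at 0.5 to 0.7, small at 0.8, nil near 0.9. Different laboratory measures may well sit at different points in that range. Including sex is justified because it is part of the design; its gain cannot be quantified from the article.

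Second, the sentence on cumulative toxicity is attached to the wrong test. This is the more consequential part, because it affects interpretation and not just efficiency. The 28%, 53% and 92% figures rest on assumed shared drifts of 0.2, 0.3 and 0.5 SD, r = 0.7, and a correlation that is the same between all pairs of visits. The qualitative result, that a time-only test responds to movement shared with placebo and a group-by-time test does not, needs none of those values.

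Neither part threatens the validity of the trial. Both are worth correcting because correction is nearly free.

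**What to change.** 1. Rest any reading of cumulative toxicity on the linear group-by-time contrast of the mixed model already planned, reported with its confidence interval. Keep the time-only trend as a description of how the measures moved overall, with no toxicity reading attached.
2. Replace the t tests on change by analysis of covariance with baseline value and sex as covariates. Alternatively, take the week-8 and earlier group contrasts from one mixed model per measure containing baseline, sex, group, visit and group by visit. Apply the same to the PROMIS-29 and biomarker comparisons that inherit this plan.

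The cost is a change of analysis wording before unmasking and two degrees of freedom (22 to 20 at 12 per arm). No data, visits or participants are added. At r = 0.9, where adjustment brings no gain, calculated power is 79.7% with both covariates against 80% for the t test.

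### Two consecutive paragraphs give different data-driven routes to the scale and test for the same laboratory comparison; the conflict matters for skewed analytes only

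*Protocol article*

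**What the plan says.** All of this stands in the protocol article under Laboratory analysis outcomes {12}, statistical methods {20a, 20b, 20c}.

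- **Second paragraph, the comparison.** "The primary outcome metric for comparison between study groups is the mean change from baseline to week 8". It adds that "all parameters will be similarly evaluated at each follow-up time point" and that "Comparisons at a single follow-up will use 2-sided independent *t* tests". A linear mixed model over time points is also specified.
- **Third paragraph, rule A.** "All distributions will be tested for skew and transformed (e.g., natural log transformed) as needed to reduce the influence of skew in subsequent analyses". The rank test is the last resort: "If inspection of distributions indicates significant non-normality that cannot be corrected with standard transformations".
- **Fourth paragraph, rule B.** For each laboratory parameter the results are described as "presenting means and confidence intervals (CI) for the change in each group, as well as the mean CI for the difference between groups". The significance test is a two-sided unpaired t test or, "if inspection of distributions indicates strong non-normality, with a non-parametric Wilcoxon signed rank test". No transformation step is mentioned, and the switch does not depend on a transformation having failed.

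Neither paragraph says which rule governs. The same section sends the PROMIS-29 scores to the plan for laboratory markers, and the secondary biomarkers to the skew adjustments of the primary analysis, so both inherit the ambiguity.

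**The concern.** Rules A and B address one quantity, the between-group difference in change from baseline for each laboratory parameter, which at week 8 is the primary metric. They differ in trigger (uncorrectable non-normality against strong non-normality) and in route (transform first against straight to ranks). An analyst following either paragraph would be following the protocol, and the two could report different p-values on different scales for the same data.

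There are two related weaknesses. Nothing ties an analyte to one scale at all visits, although each visit is compared separately and a mixed model spans them all. And both fallback sentences name the Wilcoxon signed rank test, a paired or one-sample procedure, for a comparison of two independent groups.

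At stake is whether the primary laboratory result for a skewed analyte is uniquely defined, and whether its visit-wise estimates agree with the mixed model.

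**Working it through.** **1. Source of the sample size used below.** The Sample size section gives 12 per group. The control rate is not stated. With 5% against 55%, n = [1.96·√(2·0.30·0.70) + 0.84·√(0.05·0.95 + 0.55·0.45)]² / 0.50² ≈ 11.9, so 12 per arm (power 80.2%). Then 12/(1 − 0.25) = 16 enrolled per arm. The figure reproduces at that low control rate; the present point uses it only as the number per arm.

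**2. The two rules side by side.**

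| Data for one analyte | Rule A (third paragraph) | Rule B (fourth paragraph) |
|---|---|---|
| No marked skew | t test, untransformed | t test, untransformed |
| Skewed, corrected by a log | t test, log scale | rank test if judged strong, otherwise t test, untransformed |
| Skewed, not corrected | rank test | rank test |

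The conflict is confined to the middle row.

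**3. How often it bites.** The documents give no SD for any analyte, so this is a simulation under assumptions:
- a log-normal analyte at baseline and four follow-up visits;
- correlation between visits 0.6 to 0.8;
- rule A applied as a skewness test on values, rule B as a Shapiro–Wilk test on within-arm change residuals, both at 0.05;
- a two-sample rank test as fallback, in place of the signed rank test named;
- 1,500 to 3,000 trials per setting where the run count is on record.

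The true effect, where used, is d = 1.2 on the log change. With 12 per arm the non-centrality is 1.2·√(12/2) = 2.94 on 22 degrees of freedom (critical value 2.07), which gives power of about 80%.

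| Assumed spread, 12 per arm | Different scale or test at week 8 | Opposite verdict, no effect | Opposite verdict, d = 1.2 |
|---|---|---|---|
| log-SD 0.02–0.10 | 5–8% | at most 0.5% | at most 0.5% |
| log-SD 0.2–0.5 | 20–62% | 0.4–2.2% | not run |
| log-SD 0.25–0.8, correlation 0.6–0.8 | 30–91% | 1–4% | 2–12% |
| log-SD 0.25–0.8, correlation 0.7 | 43–99% | 1–4% | 3–14% |

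The rows come from separate runs, and the spread between them shows the sensitivity to settings the protocol leaves open. At log-SD 0.25 alone, one run gave only 0.3% (no effect) and 1.4% (d = 1.2). The upper ends belong to log-SD near 0.8.

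**4. Error rates.** Each rule alone had type I error of about 5–6%. Taking the smaller of the two p-values gave 4.6–6.8%. A single pre-fixed scale and test gave 4.0–6.0%. Monte Carlo error is √(0.05·0.95/2,500) ≈ 0.4 percentage points.

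**5. Scale across visits.** If the skew test were run separately at each visit, the four follow-ups would have mixed raw and log scales in 34–79% of trials (log-SD 0.25–0.8) or 36–80% (log-SD 0.2–0.5, 12 or 16 per arm). This is conditional on a visit-by-visit reading that the text allows but does not state.

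**The case against.** The best defence is that this is one plan told twice. Rule A refers to later analyses, rule B follows in the next paragraph, and other outcomes are referred back to it as a single plan. Rule B's strong non-normality could then mean what remains after transformation, and nothing in it says the data are analysed untransformed. That reading is possible, but rule B does not carry the condition that makes it so, and its trigger is worded differently. The two texts still need reconciling.

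Several other points stand:
- Many listed measures (sodium, potassium, calcium, chloride, hemoglobin, hematocrit) are likely to have low spread in healthy adults, and for these the conflict hardly matters.
- Whether values or changes are transformed, and the cut-off for skew, are details an analysis plan may settle. Their absence here is not a fault, and the natural reading is that values are transformed.
- Nothing says that unmasked staff inspect the distributions.

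A reader might also infer that analytes will change scale between visits, or that a trend toward toxicity could not be read. The documents support neither. A scale change is permitted but not planned. The protocol still reports mean changes with confidence intervals, fits a mixed model over time, and compares newly abnormal percentages by Fisher's exact test, which does not depend on scale.

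**Conclusion.** The point holds in limited form. The two paragraphs state different routes for the same between-group comparison, and the protocol does not say which governs. For clearly skewed analytes (assumed log-normal, log-SD about 0.25–0.8, 12 per arm) the routes often pick a different scale or test. They reach opposite verdicts at 0.05 in about 1–4% of trials under no effect and in up to about 14% with a true effect near 80% power. At log-SD 0.10 or less, verdicts differ in at most 0.5%.

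It would be wrong to infer material false-positive inflation: even choosing the smaller p-value gave at most 6.8%. The cost is an undefined scale and test for the primary laboratory result of skewed analytes and, if scales were chosen visit by visit, visit estimates that may not match the mixed model. All sizes rest on assumed spreads and on a particular way of carrying out the inspection, since the documents give neither. That the signed rank test does not fit independent groups follows from the text alone.

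**What to change.** State one rule and use it in both paragraphs:

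1. For each analyte, fix the scale before unmasking, from baseline values pooled over arms.
2. Apply that scale to the values before taking the change from baseline.
3. Use the same scale at baseline, at every follow-up visit and in the mixed model.
4. Report any rank-based comparison alongside this analysis, not as a data-triggered replacement, and name it as a two-sample Wilcoxon rank-sum test in both sentences.

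PROMIS-29 and the secondary biomarkers then inherit the corrected rule through the existing cross-references. The change is wording only: no new data, visits or participants. The small downside is that analytes on the log scale are reported as ratios instead of differences in laboratory units.

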### Criteria for discontinuing or modifying allocated interventions {11b, 21b}

A participant may be withdrawn from the trial at any time they choose, due to adverse events or at their request. However, participants will be actively withdrawn if they demonstrate any new onset, moderate, or more severe adverse events attributable to the intervention. Participants will also be withdrawn if they have any critical value return on routine clinical laboratory measures of safety, including significant changes in blood cell counts, liver function tests, or renal function tests. The trial will be suspended if > 20% of study participants experience moderate or greater severity adverse events or laboratory abnormalities contributing to halting criteria including abnormal calcium, sodium, potassium, creatinine, or GFR; anemia; and/or abnormal elevations in bilirubin, elevated alkaline phosphatase, AST, or ALT that are persistent upon repeat testing.

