## Discussion

The main objective of the phase I XMaS trial is to examine the safety and tolerability of daily xanthohumol administration in healthy adults over an 8-week time frame. This objective will be accomplished by monitoring routine clinical laboratory parameters, assessing quality of life, and administering standardized adverse event queries throughout the study and using these data to make a composite assessment of clinical safety, with input from the FDA and NCCIH. Tolerability of xanthohumol will be assessed by monitoring the number and proportion of participants who discontinue the intervention citing adverse effects, changes in the seven health-related quality of life domains captured via the PROMIS-29 questionnaire, and the severity and duration of symptoms, for comparison between treatment and control groups.

Preclinical studies have demonstrated that xanthohumol has multiple therapeutic properties including modulating inflammatory pathways by acting as an FXR agonist and via inhibition of NFκB activation, regulation of gut permeability and bile acid metabolism by acting as an FXR modulator, and regulation of antioxidant protein expression via activation of NRF2 [7–13, 15, 51]. By regulating these transcription factors, xanthohumol may impact expression of numerous downstream genes in vivo and therefore has therapeutic promise for multiple disease states, including Crohn’s disease (Table 1). Furthermore, xanthohumol acts as a prebiotic for intestinal microbiota and, along with its bacterial metabolites, alters the gut microbiota [5]. Therefore, additional aims of the phase I XMaS trial are to collect data on biomarkers related to inflammation, gut permeability, bile acid metabolism, xanthohumol metabolism, and the impact of xanthohumol on gut microbiota to assess if these mechanisms are modified in vivo.

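### The primary week-8 per-protocol laboratory comparison loses participants withdrawn for toxicity, which biases that one result toward no harm

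*Protocol article*

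**What the plan says.** Three rules in the protocol article bear on this point.

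- Metric (laboratory outcomes and statistical methods section): "The primary outcome metric for comparison between study groups is the mean change from baseline to week 8". It applies to liver, renal, haematology and electrolyte measures taken every two weeks.
- Population (same section): "The primary analysis will be a per-protocol analysis as this trial is a phase I trial focused on clinical toxicity". The explanation that follows is: "we are investigating the clinical and mechanistic effects of the product for those participants who took the experimental agent only".
- Withdrawal (criteria for discontinuing or modifying allocated interventions): "participants will be actively withdrawn if they demonstrate any new onset, moderate, or more severe adverse events attributable to the intervention", and "Participants will also be withdrawn if they have any critical value return on routine clinical laboratory measures of safety". That section names blood counts, liver tests and renal tests, which are also primary outcome domains.

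On missing values the article says: "As a sensitivity analysis, missing laboratory data will be imputed by multiple imputation to assess the robustness of study results to imputation". It also plans supporting analyses: "all parameters will be similarly evaluated at each follow-up time point", linear mixed models over time, and percentages newly abnormal at each time point by Fisher's exact test. All adverse events are compared between groups. The Discussion describes tolerability as assessed by "monitoring the number and proportion of participants who discontinue the intervention citing adverse effects", among other measures.

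**The concern.** In an efficacy trial, a per-protocol analysis asks what the product does in those who take it as planned. In a toxicity trial, stopping early can itself be the result being sought. Here the link is direct: a bad enough value in a primary outcome domain is what triggers withdrawal, so the comparison is made among those who did not have one. The phase I focus on toxicity, given as the reason for per-protocol, is a reason against it.

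The resulting bias runs toward no difference and grows with the number withdrawn for harm. The article says these laboratory results will guide expectations in Crohn's disease, a population it describes as potentially vulnerable to anaemia, liver toxicity and renal abnormalities. The primary comparison should not be the one from which the most affected participants are missing.

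**Working it through.** **1. The plan's own figures.** Enrolment: 12 / (1 − 0.25) = 16 per arm, as stated. The 12 per group for a 50-percentage-point difference (chi-squared, two-sided 0.05, 80% power) needs a control rate, which the article does not give. Assumed rates of 0%, 5% and 10% yield 11, 12 and 14 per arm, so 12 is reproduced at about 5%. The point below does not depend on this, except that 4 of 16 can leave an arm and the planned 12 remain.

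**2. Does a participant withdrawn at week 2, 4 or 6 reach the primary comparison?** The article does not define the per-protocol set, so both readings need checking.

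- If it means adherent completers, the participant is outside the set.
- If it means anyone who took the product, the participant is in the set but has no week-8 value after withdrawal, and a t test of week-8 change drops them.

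The article does not call for a week-8 sample after withdrawal. One taken then would be off product and need not reflect the on-treatment change. The answer is no under either reading.

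**3. Illustration on assumed values.** The article gives no toxicity rate, no standard deviation (SD) and no threshold for a critical value. Assume 16 per arm, 4 on xanthohumol with an ALT rise of 60 U/L who are withdrawn at week 4, and no change in the other 28.

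- Week-8 completers: 0 (12 on xanthohumol) − 0 (16 on placebo) = 0 U/L.
- Last on-treatment values counted: (4 × 60 + 12 × 0) / 16 − 0 = +15 U/L.
- If only 2 of the 4 are withdrawn: completers show 2 × 60 / 14 = 8.6 U/L, still short of 15.

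**4. Simulation on assumed values.** 5,000 trials per scenario, 16 per arm, unit-SD change scores, two-sided t test at 0.05. All harmed participants are on xanthohumol. They are either kept with their shift or removed before week 8.

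| Harmed, shift | Mean difference, kept | Mean difference, removed | Rejection, kept | Rejection, removed |
|---|---|---|---|---|
| 2 of 16, 3 SD | 0.38 SD | 0.00 SD | 8% | 5% |
| 4 of 16, 3 SD | 0.74 SD | −0.01 SD | 26% | 5% |
| 4 of 16, 5 SD | 1.26 SD | 0.01 SD | 41% | 5% |
| 6 of 16, 5 SD | 1.88 SD | 0.00 SD | 87% | 4% |

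**5. Would the halting rules catch it?** Not necessarily. Over full enrolment, 4 / 32 = 12.5% and 6 / 32 = 18.75%. Both lie below the 20% suspension figure in the discontinuation section and the 25% figure in the sample size section. With the smaller denominators of an interim look, a rule could be met sooner.

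**The case against.** The best reply is that the safety conclusion does not rest on this one test. In the illustration, a week-4 comparison that includes the four participants would show them, as would the mixed models, the newly abnormal percentages, the adverse event comparison, the discontinuation counts and the monitoring board's review. The Discussion speaks of a composite assessment of safety. All of this stands, and it rules out several stronger readings.

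- A reader might infer that harm would go unseen in the trial. The analyses just listed contradict that.
- A reader might infer that the 80% adherence limit defines the per-protocol set, so that anyone who skips capsules because of symptoms is also excluded. The adherence section does not say so; the link is an assumption.
- A reader might infer that per-protocol also removes discontinuations and adverse events from the tolerability assessment. The sentence stands in a paragraph on laboratory measures, and nothing extends it to those outcomes.
- A reader might set 0/12 abnormal per-protocol against 4/16 among all treated. That needs the per-protocol restriction to apply to the by-visit proportions too, which the article does not state.

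Two technical replies also have force. Multiple imputation could recover part of the signal from earlier visits. Standard imputation assumes data missing at random, but so does a mixed model, so that assumption cannot be held against one and not the other. It is comparatively plausible when a recorded critical value triggers the withdrawal. Still, imputation is only a sensitivity analysis here, and the article does not say whether it brings back participants outside the set. Second, keeping everyone restores the estimate more than the power: Fisher's exact test on 4/16 against 0/16 gives a two-sided p of about 0.10, and rejection with everyone kept is only 8% to 41% in three of the four scenarios.

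**Conclusion.** The concern holds for the primary laboratory comparison and only there. The stated metric, population and withdrawal rules together remove participants withdrawn for toxicity before week 8, whichever way per-protocol is read, and bias that result toward no harm. This is a choice the article states and justifies, not detail left to an analysis plan.

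The direction of the bias follows from the rules, provided withdrawals for toxicity occur more often on xanthohumol. Its size is not known. The 0 against +15 U/L contrast assumes four withdrawals, a 60 U/L rise that leads to withdrawal, no change in anyone else, and last values carried to week 8. The simulated loss of 0.4 to 1.9 SD likewise rests on assumed rates and shifts. Milder abnormalities that do not lead to withdrawal stay in the comparison.

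**What to change.** Before unmasking, make the primary safety population all randomised participants who took at least one dose, analysed by product received. Use every post-baseline laboratory value up to and including the withdrawal visit, in two forms:

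- per participant, the proportion with any newly abnormal post-baseline value (or the worst post-baseline change), which does not need a week-8 value;
- for mean change, the mixed model over all visits, with its missing-at-random assumption stated. It will not necessarily return the carried-forward +15 U/L of the illustration.

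Report withdrawals by arm and reason next to these results. Keep per-protocol as a supportive analysis and for the mechanistic biomarkers, and define the set, including whether the 80% adherence limit applies. The withdrawal rules stay as they are.

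The cost is a change of wording, with no new participants or samples; the mixed model and two-weekly values are already planned. The downside is slight dilution of mean effects by non-adherent participants.
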